### **8.3.2 Body Mass Index (BMI):**

BMI of all the participants will be assessed at diagnosis, prior to start of treatment, then at 3-, 6-, 9- and 12- month study visit. Height will be measured using a Harpenden stadiometer and weight will be measured using electronic scales (as per standard practice).

BMI will be derived from the formula:-

BMI = weight (kg) / height (m^2)

Standard deviation scores (SDS) for BMI will be derived from the UK 1990 standards (31) .

## 8.4 Other Assessments

Quality of Life (PedsQL; see section 8.4.1) and Health Status instrument (HUI2/3; see section 8.4.2) have been combined into age appropriate questionnaire booklets for ease of administration.

| Time Points     | Children Aged      | Questionnaire booklet administration completed by |                                         |
|-----------------|--------------------|---------------------------------------------------|-----------------------------------------|
|                 |                    | Parent/carer                                      | Child                                   |
| Baseline,       | 3 years – 11 years | Booklet 3 –15 years (HUI2/3)                      | -                                       |
|                 | 12 years -15 years | Booklet 3-15 years (HUI2/3)                       | Booklet 12-15 years (HUI2/3)            |
| 3 and 9 months  | 3 years – 11 years | Booklet 3 –16 years (HUI2/3)                      | -                                       |
|                 | 12 years -16 years | Booklet 3-16 years (HUI2/3)                       | Booklet 12-16 years (HUI2/3)            |
| 6 and 12 months | 2 years            | Booklet 2 years (PedsQL)                          | -                                       |
|                 | 3 years-4 years    | Booklet 3-4 years (PedsQL and HUI2/3)             | -                                       |
|                 | 5 years – 7 years  | Booklet 5-7 years (PedsQL and HUI2/3)             | Booklet 5-7 years (PedsQL)              |
|                 | 8 years – 11 years | Booklet 8-12 years (PedsQL and HUI2/3)            | Booklet 8-11 years (PedsQL)             |
|                 | 12 years           | Booklet 8-12 years (PedsQL and HUI2/3)            | Booklet 12 years (PedsQL and HUI2/3)    |
|                 | 13 years -16 years | Booklet 13-16 years (PedsQL and HUI2/3)           | Booklet 13-16 years (PedsQL and HUI2/3) |

### 8.4.1 Quality of Life

Quality of Life (QoL) will be assessed using validated diabetes specific QoL (PedsQL) questionnaire instruments (32) at 6- and 12-months after diagnosis. Children and young people aged 5-7 years, 8-12 years and 13-16 years will use developmentally appropriate versions and the parental version will be used for all age groups (32). The instrument has been reported as offering the optimal clinical utility when compared to other diabetes-specific instruments in this age group (33).

#### **8.4.2 Health Economics analysis:**

The economic analysis will adopt the perspective of the NHS by measuring healthcare resource use and costs including those associated with both technologies, CSII (purchase, maintenance and use of disposables) and MDI; those associated with adverse events, any necessary investigations, procedures, treatments and hospitalisations; insulin and other medicines; and contact with health professionals.

##### **Data collection**

- Resource use will be collected prospectively within participants' CRFs. Participants' use of other services will be collected by means of a health resource use questionnaire collected by the RN in interview with the participant prior to start of randomised treatment (for the previous 3-months) then at 3-, 6-, -9 and 12-months study visits.
- Data from Patient Administration Systems will be requested. The trial health economist will contact the Finance departments, Information Technology and Patient Administration Departments of each recruiting centre to inform them of SCIPi, and that a future request will be made for data on trial participants' healthcare resource use. 12-months after randomisation of the last patient at each recruiting centre, the trial health economist will contact the Finance departments of each centre, and submit a request (via the MC-CTU, to maintain patient anonymity) for: Ward name; ward speciality (e.g. paediatric, paediatric ICU, etc.); the average cost per bed day on the ward; and the financial year the costs refer to. The health economist will also contact the Information Technology or Patient Administration Departments of each centre and submit a request (via the MC-CTU, to maintain patient anonymity), for: ward name; ward speciality (if possible); start date on the ward; end date on the ward; number of occupied bed days on the ward.
- Unit cost data will be obtained from a variety of sources, including routine hospital data (NHS reference costs) and nationally published data (34).
- Health utilities will be assessed prior to start of the treatment then at 3-, 6-, -9 and 12-months study visits. This will be accomplished by administering the Health Utilities Index Mark 2 and 3 -HUI23P1En.15Q questionnaire to the parents/carers of all the participants and HUI23S1EN.15Q questionnaire to the participants of 12 years and over. The HUI2/3 has been validated for use in children (35) and is the preferred instrument for this purpose (36). The six attributes of the HUI2/3 (sensation, mobility, emotion, cognition, self-care, and pain) will be summarized into a single UK-derived preference-based utility score (37).

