## 6 ENROLMENT AND RANDOMISATION

### 6.1 Screening

All patients who are newly diagnosed with T1DM aged 7 months -15 years (inclusive) at the study centres will be screened to identify potentially eligible participants for the study.

Potentially eligible participants (i.e. those that meet the eligibility criteria listed in section 5) and their parent or legally acceptable representative will be invited to participate in the study and provided with the patient information sheet and consent form. The family will be allowed sufficient time to discuss the trial and decide whether to consent to trial entry (see section 11.3 for consent procedures). Providing information, discussing the study and obtaining informed consent should occur as close to the time of diagnosis as possible, ideally between the time of diagnosis (Day 0) and Day 5. Once consented, baseline data should be collected, the participant should be randomised (see section 6.2 and 6.3) and the randomised treatment should be started within 14 days of diagnosis (see section 7).

A 'Screening log' will be maintained of all the patients who undergo screening regardless of whether they decide to participate in the study. Reasons for not being eligible and timelines for providing information and approaching the patient for consent will be recorded. Reasons for declining to participate will be asked routinely but it will be made clear that patients, parents or carers do not have to provide a reason unless happy to do so.

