### 6.3 Randomisation

Participants will be randomised to receive either MDI or CSII (in a 1:1 ratio) once:

- a. Eligibility criteria has been fulfilled;
- b. Fully informed written proxy consent has been obtained;
- c. Baseline assessments have been completed.

Participants will be randomised using a secure (24-hour) web based randomisation programme controlled centrally by the MC-CTU. Personal login username and password, provided by the MC-CTU, will be required to access the randomisation system. When consent eligibility and participant age have been confirmed the participant treatment allocation and a unique study number (randomisation number) will be displayed on a secure webpage and an automated email confirmation will be sent to the authorised randomiser, Principal Investigator (PI) and trial coordinator. It is the responsibility of the PI or delegated research staff to inform the pharmacy department at their centre prior to randomisation to ensure there is sufficient supply of the study treatments. For further details on randomisation see section 9.2.

---

 When RN is referred to in this protocol it means either the diabetes research nurse or member of the research team who has been delegated that duty.

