|              |                                                           | Diagnosis                                                                         | Prior to start of treatment |                                                                              |               |               |                |
|              |                                                           | T0 =
Randomisation
(randomisation will be made within 14 days of diagnosis) |                             | (T0+3 months)                                                                | (T0+6 months) | (T0+9 months) | (T0+12 months) |
|              | Participant completed Health Utilities Index Mark 2 and 3 |                                                                                   | (X)                         | (X)                                                                          | (X)           | (X)           | (X)            |
|              | Parent completed Health Utilities Index Mark 2 and 3      |                                                                                   | X                           | X                                                                            | X             | X             | X              |
| Resource Use | RN completed CRF                                          |                                                                                   | X                           | X                                                                            | X             | X             | X              |

(X) – As indicated/appropriate.

1- Providing information, discussing the study and obtaining informed consent should occur as close to the time of diagnosis as possible, ideally between the time of diagnosis and Day 5 (diagnosis date +5).

2 - Measurement of blood glucose will be done by a glucose test at the time of diagnosis and measured as per local policy and the results recorded from patient medical records. It is measured by glucometer at remaining time points (refer section 8.2.3).

3 - Study Intervention –Randomised treatment should be commenced within 14 days of diagnosis

4– Hb1Ac will be collected and analysed according to local clinical practice and a sample sent for central analysis.

5 - Routine clinical tests will be conducted as part of routine clinical management and where appropriate results recorded from patient medical records.

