## **9.7 Economic analysis**

The primary economic analysis will be based on an assessment of the incremental costs per QALY gained. Additionally, a cost-consequences analysis will be performed based on the primary and secondary outcome measures. Costs and benefits will be discounted at an annual rate of 3.5% (36).

ICERs will be estimated, with uncertainty in parameter estimates being addressed through the application of bootstrapping and the estimation of cost-effectiveness acceptability curves (38). A regression analysis of cost and QALYs, with age, baseline HbA1c, utility (39) and other covariates as deemed appropriate, will be conducted to conserve any correlation between costs and benefits, and minimise bias in the cost utility estimate. Estimates of ICERs will be compared with the £20,000 to £30,000 per QALY threshold of cost-effectiveness set by NICE (1), and a range of univariate and probabilistic sensitivity analyses will be conducted to assess the robustness of the analysis. Additionally, trial results will be extrapolated to estimate lifetime costs and benefits to avoid time horizon selection bias, and to capture long-term micro- and macrovascular complications. We will approach IMS Health for permission to use the CORE diabetes model (40) and parameterise with estimates derived from the trial.

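### Timing of baseline health utility is inconsistent: sections 6.1 and 6.3 put baseline assessments before randomisation, but Table 1 and section 8.4.2 tie the HUI2/3 only to the start of treatment

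*Protocol*

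**What the plan says.** Two sets of passages in the protocol deal with the timing of baseline data.

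**Before randomisation.** Section 6.1 gives the order: "Once consented, baseline data should be collected, the participant should be randomised", with treatment afterwards. Section 6.3 makes it a condition of randomising, item (c): "Baseline assessments have been completed". The introduction to section 8 names the baseline case report form ahead of randomisation. Section 8.4 lists the HUI2/3 booklets under the baseline time point.

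**Before treatment.** Section 8.4.2 says of the HUI2/3: "Health utilities will be assessed prior to start of the treatment then at 3-, 6-, -9 and 12-months study visits". It places the resource-use questionnaire "in interview with the participant prior to start of randomised treatment (for the previous 3-months" of use). Table 1 divides baseline into two columns, one for diagnosis and randomisation and one for the period before treatment starts. The row "Parent completed Health Utilities Index Mark 2 and 3", the participant HUI2/3 row and the resource-use row are marked only in the second. The only other mark in that column is the study intervention, whose footnote reads "Study Intervention –Randomised treatment should be commenced within 14 days of diagnosis". Section 7.1 refers sites to Table 1 for what must be done before randomised treatment begins.

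**Use of the data.** Section 9.7 makes incremental cost per QALY the primary economic analysis and plans "A regression analysis of cost and QALYs, with age, baseline HbA1c, utility (39) and other covariates as deemed appropriate". The reference cited at that point concerns controlling for baseline utility when estimating mean QALYs.

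**The concern.** The trial is open label, and the allocation appears on screen to site staff at randomisation. The HUI2/3 is completed by parents, and also by participants aged 12 and over. A site working from Table 1 and section 8.4.2 could hand out the booklet after the family has learned whether the child will have a pump or injections, and would still be following those two passages.

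A baseline covariate is safe to adjust for because allocation cannot have changed it. Utility reported after allocation is known does not have that property. If knowing the arm alters the answers, adjustment removes or adds something that is not a chance baseline imbalance. The same value is normally also the starting point of the QALY curve. At stake are the adjusted QALY difference and the ICER, which section 2.2 intends to inform NHS investment.

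**Working it through.** The point turns on the order of events. No figure in the protocol depends on it, so there is nothing to reproduce. The passages are set side by side instead.

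| Place | Baseline HUI2/3 or baseline data tied to |
|---|---|
| 6.1 | after consent, before randomisation |
| 6.3(c) | complete before randomisation |
| 8, introduction | baseline form, then randomisation |
| 8.4 | baseline, with no finer timing |
| 8.4.2 | start of treatment |
| Table 1 | pre-treatment column, not the column with the randomisation mark |

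**Step 1. Is there a gap between randomisation and treatment?** Consent is ideally obtained by Day 5 and treatment starts within 14 days of diagnosis. A child consented and randomised on Day 5 could wait up to 14 − 5 = 9 days. Training on the pump is given only to the CSII arm. The interval is real.

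**Step 2. Does anything enforce 6.3(c)?** As section 6.3 describes the web system, allocation is displayed once consent, eligibility and age are confirmed. Completion of the baseline questionnaire is not among the checks listed.

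**Step 3. Is the timing phrase decisive by itself?** No. Section 8.2.1 uses almost the same phrase for HbA1c, yet Table 1 marks baseline HbA1c in the diagnosis and randomisation column. For the HUI2/3 and resource use, phrase and column both point to the start of treatment.

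**Step 4. Does the value enter the analysis?** For utility, yes: section 9.7 names it. Baseline resource use is not named and could enter only among the unspecified further covariates.

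**Step 5. What would a shift do?** Let *d* be the between-arm difference in reported baseline utility caused solely by knowing the allocation, and *b* the regression slope of QALYs on baseline utility. Assume the QALY is the area under the utility curve by the trapezoidal rule. The first interval is 3 months, or 0.25 year, so baseline carries weight 0.25/2 = 1/8. Then

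bias in adjusted QALY difference = *d*/8 − *b* × *d* = *d* × (1/8 − *b*).

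This is zero when *b* = 1/8 and grows in size as *b* rises above it. The protocol gives neither *d* nor *b*. Purely to show the mechanism, assume *d* from 0.01 to 0.05 and *b* from 0.125 to 0.6. The result then runs from 0.01 × (0.125 − 0.125) = 0 to 0.05 × (0.125 − 0.6) = −0.024 QALY. These inputs are assumptions, so the range is not an estimate for this trial.

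**The case against.** The strongest reply is that the protocol already contains the rule. Section 6.3(c) is a condition of randomising, section 6.1 and the introduction to section 8 give the same order, and both section 8.4 and the header of Table 1 call the HUI2/3 a baseline item. Anything done before randomisation is also done before treatment, so section 8.4.2 is less specific than 6.3(c) but compatible with it. In the original layout the randomisation label in Table 1 may span both baseline columns, which the extracted text cannot settle.

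Most of this stands, and it limits the point. A reader might infer that the protocol schedules utility collection after randomisation. It does not: later collection is left open, not prescribed. The reply does not remove the inconsistency, because Table 1 separates these forms from every other baseline measurement and groups them with the start of the intervention, and sections 6.2 and 7.1 both send sites to that table.

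Four further inferences should not be drawn:

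- **Strong preferences in these families.** Section 2.2 describes preference in children with established diabetes and gives it as the reason for recruiting at diagnosis. It does not show strong preference in this population.
- **Baseline resource use as a named adjuster.** Section 9.7 does not list it.
- **Bias in change in BMI SDS.** Section 8.3.2 says BMI "will be assessed at diagnosis, prior to start of treatment" and then at the visits, which can be read as one baseline reading or two. Table 1 shows one baseline height and weight mark. Nothing in the document makes a post-randomisation reading the baseline or gives the arms different waits.
- **A monetary size.** It would rest wholly on assumed inputs.

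**Conclusion.** The point holds as an inconsistency in timing. Sections 6.1 and 6.3(c) require baseline assessments before randomisation, while Table 1 and section 8.4.2 do not hold the HUI2/3 to that. Collection with knowledge of the allocation is possible, and the value goes into the regression for the primary economic analysis.

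The size of any bias cannot be estimated from the document and could be nil. It needs two things the protocol does not establish: that some sites collect the questionnaire after allocation, and that knowing the arm changes the answers. The consequence is confined to the economic evaluation. The primary HbA1c comparison is unaffected. The correction is still worth making because it costs little and applies the protocol's own rule.

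**What to change.** 1. In Table 1 and section 8.4.2, state that the baseline HUI2/3 is completed after consent and before randomisation, in line with section 6.3(c). Time the baseline resource-use interview the same way for consistency.
2. In section 9.7, state that only utility measured before randomisation is used as the baseline covariate.
3. As a tidying edit, word section 8.3.2 to match the single baseline height and weight mark in Table 1.

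The cost is a table and wording change. The same forms are used and no assessment is added; the booklet and interview are completed before the allocation is opened. For children already randomised, section 13.2 has the questionnaire cover record the dates given and completed. Comparing these with the randomisation date would show which forms were late, except for those completed on the day of randomisation.

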#### **8.5 Loss to Follow-up**

If any of the trial participants are lost to follow up, contact will initially be attempted through the PI or delegated research staff at each centre. If the lead investigator at the trial centre is not the participant's usual clinician responsible for their specialist care then follow up will also be attempted through this latter clinician. Where these attempts are unsuccessful, the participants GP or the child's local diabetic service will be asked to contact the participant or the participant's family to provide follow up information to the recruiting centre. Consent will be sought to contact the participants GP. Wherever possible, information on the reason for loss to follow up will be recorded.

## **8.6 Trial Closure**

The end of the trial is defined to be the date on which data for all participants is frozen and data entry privileges are withdrawn from the trial database. However, the trial may be closed prematurely by the Trial Steering Committee (TSC), on the recommendation of the Independent Data and Safety Monitoring Committee (ISDMC).

## **9 STATISTICAL CONSIDERATIONS**

### **9.1 Introduction**

A separate and full Statistical Analysis Plan (SAP) will be developed prior to the final analysis of the trial. The SAP will be agreed by the Trial Steering Committee (TSC). The main features of these planned statistical analyses are included here in the protocol.

### **9.2 Method of Randomisation**

Participants will be remotely randomised in a 1:1 ratio using a web service. The randomisation code list will be generated by a statistician using block randomisation with random variable block size method at the MC-CTU. Participants will be randomised to either MDI or CSII treatment in a ratio of 1:1 and will be stratified by centre and age.

### **9.3 Outcome Measures**

The primary and secondary outcomes are provided in section 4.2. Outcomes may be presented as mmol or the equivalent %.

### **9.4 Sample Size**

#### **Internal pilot**

Thirty subjects will be recruited. 30 patients provides 80% power to detect a drop in the consent rate to 25% from the assumed 50%, at the 5% significance level.

#### **Full Trial**

A sample size of 143 in each group will have 80% power to detect a difference in means of 0.50 assuming that the common standard deviation is 1.50 using a two group t-test with a 0.05 two-sided significance level. Allowing for 10% loss to follow up means we would need a total of 316 participants (158 per group). The estimate used for the standard deviation in the sample size calculation was taken from an audit at Alder Hey Children's NHS Foundation Trust based on children matching the inclusion criteria for this proposed study. A difference in HbA1c of 0.5% is widely recognized as the threshold used by the Food and Drug Administration (FDA) and pharmaceutical industry to determine effectiveness of any new oral hypoglycaemic agents. Current national studies investigating therapeutic interventions in children with diabetes were powered using this effect size. An improvement of 0.61% was detected in adults in the meta-analysis of studies included in the 2004 HTA report suggesting that in addition to this estimate being the minimum clinically important it is also a realistic difference to detect.

